### Study population

The study population will include all resident PWH and PWoH, 18 years or older, born between 1940 and 2008, who resided in Sweden at any time point between 1983 and 2024. The study period will span from 1 January 1983 to 31 December 2024. The inclusion date will be the day the person turns 18, the start date of residency in Sweden, or the study start date, whichever occurs last. Follow-up will continue until emigration, death, end of study time or until 6 months before the first incident of CRC. The outcome of interest is CRC. See figure 1 for an illustration of the inclusion criteria and how inclusion and the follow-up period were defined.

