#### Data preparation

For this study, we will use complete cases only since missing data are minimal. Variables missing more than 10% of the data will be omitted, and after that, any observations with missing data will be dropped.^32^ For the ML analyses, the data will be split 80% into training and 20% into test sets based on follow-up time. The variables in each set will be further prepared to optimise their analysis. Categorical variables will be transformed using one-hot encoding. Normalisation and standardisation of variables will be applied where necessary.

The participants will be matched 1:10 using the entire HIV-negative population in Sweden that fit the criteria. They will be matched on age, legal sex, region of birth and comorbidities including hypertension, chronic obstructive pulmonary disease, diabetes and previous cancer diagnosis.^33
34^ The standardised mean difference of the cohorts will be compared from before and after matching to confirm consistency. Power was calculated using the full anticipated study population consisting of just over 13 000 PWH matched 1:10 to approximately 130 000 PWoH. Median follow-up time is estimated to be at least 10 years in both groups. The expected incidence rate of CRC used for the calculation was the Swedish age-standardised incidence rate reported by the European Commission (129.1 per 100 000 population).^35^ Based on these assumptions and using a two-sided alpha of 0.05, the study is estimated to have 80% power to detect an HR of approximately 1.20 or greater.

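### The stated 80% power at HR 1.20 is not reproduced at 10 years of follow-up, the only duration given: power there is about 62–69%, and 80% is reached at HR about 1.23–1.25

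*Protocol article*

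**What the plan says.** The power statement is in the Data preparation part of the protocol article's Data analysis plan. Its inputs are:

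- Group sizes: "full anticipated study population consisting of just over 13 000 PWH", "matched 1:10 to approximately 130 000 PWoH".
- Follow-up: "Median follow-up time is estimated to be at least 10 years in both groups".
- Event rate: "the Swedish age-standardised incidence rate reported by the European Commission (129.1 per 100 000 population").
- Test level: "using a two-sided alpha of 0.05".

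The result is presented as resting on those assumptions: "the study is estimated to have 80% power to detect an HR of approximately 1.20 or greater". The article gives no event count, mean follow-up, total person-years, formula or software for the calculation, and does not say whether the rate applies to PWH, PWoH or everyone. The Study population section adds the time frame: "The study period will span from 1 January 1983 to 31 December 2024".

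**The concern.** A power figure published with its inputs should be recoverable from them, at least approximately. Here a direct calculation at 10 years gives roughly a third fewer events than Schoenfeld's formula requires for HR 1.20. Either 10 years was used and the detectable HR is stated too favourably, or a longer follow-up was used and the reader has not been told what it was.

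The stake is limited. The study takes all eligible PWH in Sweden, so no recruitment decision depends on the figure. But this is the only quantitative justification of study size in the article, and a reader cannot tell which hazard ratio it supports.

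**Working it through.** **Inputs.** From Data preparation: 13 000 PWH, 130 000 PWoH (PWH share 1/11), rate 129.1 per 100 000, two-sided alpha 0.05, target power 80%, HR 1.20. Two assumptions are added: the rate is per year, and each person contributes 10 years on average.

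**Step 1: events needed for the stated figure (Schoenfeld).**

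D = (z₀.₉₇₅ + z₀.₈₀)² / [p(1 − p)(ln HR)²]

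= (1.960 + 0.8416)² / [(1/11)(10/11)(0.1823)²]

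= 7.849 / (0.08264 × 0.03324) ≈ 2 857 events.

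**Step 2: events available at 10 years.**

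- Rate applied to everyone: 143 000 × 0.001291 × 10 = 1 846.
- Rate applied to PWoH, with 1.2 times that rate in PWH: 13 000 × 1.2 × 0.001291 × 10 = 201, plus 130 000 × 0.001291 × 10 = 1 678, in all 1 880.

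The shortfall against 2 857 is about one third (1 880 / 2 857 = 0.66).

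**Step 3: power at HR 1.20 with 10 years.**

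- Schoenfeld, 1 880 events: Φ(√(1 880 × 0.08264) × 0.1823 − 1.960) = Φ(2.272 − 1.960) = 62.3%. With 1 846 events it is 61.5%.
- Wald test of the log rate ratio: standard error √(1/201.4 + 1/1 678.3) = 0.0746, so Φ(0.1823/0.0746 − 1.960) = Φ(2.445 − 1.960) = 68.6%.
- Other two-sided variants lie between these or close to the upper one: two proportions 67–68%, score test 67.5%, Freedman 68–69%.

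None comes within 10 points of 80%. If 129.1 is assigned to PWH instead of PWoH, power is lower still, at about 55% (Schoenfeld) to 61% (Freedman).

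**Step 4: HR detectable with 80% power at 10 years.** Solving the same formulas for HR gives 1.251 (Schoenfeld), 1.235 (score) and 1.230 (Wald).

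**Step 5: mean follow-up that would deliver 80% at HR 1.20** (rate applied to PWoH).

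| Formula | Mean years needed |
|---|---|
| Wald | 13.1 |
| Score | just under 14 |
| Schoenfeld | 15.2 (2 857 / 1 880 × 10) |

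**Step 6: can a median of 10 years go with such a mean?** Yes. As an illustration, exponentially distributed follow-up with median 10 has mean 10 / ln 2 = 14.4 years. Power at HR 1.20 is then 78% (Schoenfeld) to 84% (Wald, Freedman), and the detectable HR is 1.21 to 1.19.

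**Step 7: could sidedness explain it?** One-sided 5% at 10 years gives 73–79% at HR 1.20, near the stated value by Wald or Freedman, but the text specifies a two-sided test.

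**The case against.** The strongest reply is that the text gives a floor on a median, not a mean. Expected events depend on total person-years, and a 42-year window with staggered entry could easily give a mean well above the median. Step 6 shows that a median of exactly 10 years is compatible with a detectable HR that is fairly called approximately 1.20. This stands. A reader might infer that the inputs prove power of only 62–69%. They do not, because they leave the person-years open.

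A reader might also infer more than the documents support in other ways:

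- That 15.2 years of mean follow-up is the only way to reach the figure. That value is specific to Schoenfeld's formula; the Wald calculation needs 13.1.
- That 129.1 is too high for this cohort. The article does not give the reference population behind the rate or the cohort's distribution of person-years by age, so neither the direction nor the size of any bias can be established.
- That a null HIV effect would be over-interpreted. The aims are prediction and comparison of model performance, and the article specifies no test of an HIV hazard ratio.
- That the number of CRC events in the test set can be taken as 20% of the total. The 80/20 split is based on follow-up time, so that proportion need not hold.

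What the reply does not remove is the gap itself. The mean required is about 31% to 52% above the one duration given, and no stated quantity fills that gap. The word approximately does not cover it either: an HR of 1.23–1.25 is an excess hazard 15–25% larger than that of 1.20.

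**Conclusion.** The point holds in a limited form. At 10 years per person, no standard two-sided formula that was tried reproduces 80% power at HR 1.20. Power is about 62–69%, that is 11 to 18 points short, and 80% is reached at HR about 1.23–1.25. The published figure requires an unstated mean follow-up of about 13 to 15 years, which the text permits but does not establish.

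This rests on reading 129.1 per 100 000 as an annual rate, applied to PWoH or to the whole cohort, and on the rounded group sizes. Confidence is high in the 10-year arithmetic. Whether the actual study has less than 80% power at 1.20 cannot be decided from the article. This is an error or omission in a reported calculation, not a flaw in the design.

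**What to change.** Establish which follow-up entered the calculation, then amend the power statement in Data preparation in one of two ways:

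- If 10 years per person was used, restate the detectable HR at 80% power as about 1.23–1.25, according to the formula, and give the power at HR 1.20 as about 62–69%.
- If a longer follow-up was used, keep 1.20 but state the mean follow-up or total person-years, the expected number of CRC events, the group to which 129.1 per 100 000 was applied, and the formula.

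The cost is a sentence or two. Design, data and analysis are unchanged. Under the first option the stated detectable HR becomes less favourable.

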#### Cox PH regression

A Cox PH regression model will be used as a baseline performance comparison for the ML methods. This model will favour the simplest approach, and the use of prior knowledge supported by literature will select the most relevant variables. The model performance will then be considered to develop the model for the prediction of cancer among PWH.

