## Abstract

**Abstract:**

**Introduction:**

There are currently no colorectal cancer (CRC) screening recommendations specifically outlined for people with HIV (PWH). Screening measures used for people without HIV (PWoH) have been previously discussed as sufficient for use among PWH, despite observations of higher CRC prevalence and CRC reportedly appearing at earlier ages among PWH in comparison to PWoH. Machine learning (ML) methods are regarded as robust approaches that may enhance predictive performance, particularly in the context of complex or high-dimensional data. This study aims to develop an ensemble ML model to predict CRC risk in PWH using comprehensive nationwide datasets. The model’s predictive performance will be evaluated and compared with a baseline Cox proportional regression model. The better-performing method will be implemented to develop a CRC risk prediction model with the aim of personalising screening recommendations for PWH.

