A range of ML methods will be used for the analysis. These algorithms will cluster, classify or identify variables according to their levels of importance in predicting cancer outcomes, aiding in variable selection and prediction model development. Unsupervised ML techniques can explore extensive datasets and examine data without predefined constraints. Supervised ML techniques, however, are still capable of analysing extensive datasets, but in the presence of predefined labels. Using both methods allows for the integration of diverse results from various methodologies, which may strengthen our findings and prediction performance.^16
17^

ML methods and specifically ML prediction modelling have been previously applied to predict certain outcomes for PWH. In clinical care for PWH, ML methods have been applied to predict viral suppression among PWH^18^ and predict who is most at risk of disengaging from ART care.^19^ Similar to the aim of our project, ML methods have been previously applied to develop cancer risk prediction models, but not specifically for PWH.^20
21^ Supervised ML models have been applied to predict the occurrence of cervical precancerous lesions among PWH.^17^ ML methods have also been used to predict comorbidity outcomes as defined by the Charlson Comorbidity Index, which includes cancer, but not as an isolated outcome.^22^ These methods have not yet been applied, to our knowledge, specifically to predict the risk of CRC occurrence among PWH.

In summary, there is a need for updated recommendations and an opportunity to personalise CRC screening recommendations for PWH using robust methods of analysis. This study will aim to develop high-quality risk prediction models by applying various robust ML methods in an ensemble model and comparing it to a baseline Cox PH model. The findings will support model development and provide high-performing tools to help personalise CRC screening recommendations.

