### Data analysis plan

A detailed description of the variables of interest under study from each register is provided in online supplemental table 1. Aspects of the study will mirror the protocol applied by Fernández Carbonell and colleagues, and the code available online will be applied throughout.^16^ All data preparation and analysis will be carried out in Stata and Python using Jupyter Notebook in Visual Studio Code.

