#### ML ensemble model—unsupervised ML

Time Series Split cross-validation (CV) will be used during model training and meta-learning stages. K-means and hierarchical clustering methods will be used for the clustering analyses. The clustering analyses will be performed within each CV fold. The optimal number of clusters for the clustering analyses will be determined using both the Calinski-Harabasz Index and Silhouette Scores.^16
36^ The final number of clusters will be selected based on the estimates from these two methods and applied.

The clustering analyses will be used to observe any differences in the clustering patterns across the outcomes.^16
37
38^ These methods can uncover patterns from the data structure without prior information or further input to the analysis.^39^ By interpreting the most decisive variables during the clustering process additionally using decision trees, their importance in predicting the outcome can be evaluated in the process. K-means clustering will be used to group unlabelled data into the pre-estimated number of distinctive clusters depending on their distances from each other.^38^ The algorithm iteratively runs until there are no significant changes to the clusters. Hierarchical clustering groups two observations together which are most similar, and is iteratively updated until the pre-estimated number of distinctive clusters is reached.^37^ Decision trees will be used to aid interpretation of the clustering decisions from both analyses to determine the important contributing variables to the outcome.^16^ If a difference in the clustering patterns over the outcome is observed, we can interpret the most determining variables in the clustering patterns as potentially important to predicting the risk of developing cancer. Cluster labels will be generated from the training data only to avoid data leakage and added as variables to both the training and test sets in all models.

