#### ML ensemble model—supervised ML

Elastic Net regularisation, XGBoost, Random Survival Forests and decision trees will be used to develop the ensemble model for predicting CRC risk. For Elastic Net regularisation, a Cox PH model with an Elastic Net penalty will be used to estimate relative risk and interpret variable importance via the penalised regression coefficients. The resulting model additionally highlights influential predictors by minimising less important coefficients towards zero, indicating lower contribution to predicting the outcome.^40^

Decision trees are tree-based models that split data based on variable thresholds to make predictions. Decision trees suited for survival time-to-event data will be used. This method will estimate the probability of cancer over time. This model may additionally be used to infer how much each variable contributes to reducing dataset impurity at each split,^41^ contributing to our understanding of which variables are most valuable to the outcome prediction. Random Survival Forest models work similarly to decision trees but aggregate results across many trees, providing more robust estimates of variable importance and potentially improved performance for risk prediction. XGBoost uses built-in optimisation techniques to develop high-performing prediction models.^42^ The output of the XGBoost model may additionally be used to assess the predictive value of individual variables.

Out-of-fold predictions from each model will be stored to serve as inputs for the meta-learner. Additionally, SHapley Additive exPlanations (SHAP) values will be computed for each trained base learner to assess variable contributions and enhance model transparency.

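### The only stated Cox comparator differs from the ensemble in how its predictors are chosen as well as in algorithm, so the contrast alone cannot credit a win to machine learning

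*Protocol article*

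**What the plan says.** The Cox PH regression section gives the Cox model its role: "A Cox PH regression model will be used as a baseline performance comparison for the ML methods". It then says how the predictors are found: "This model will favour the simplest approach, and the use of prior knowledge supported by literature will select the most relevant variables". It states neither a number nor a list of covariates.

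For the ML side, the Data analysis plan refers to a supplement: "A detailed description of the variables of interest under study from each register is provided in online supplemental table 1". The only removal rule stated under Data preparation concerns missing data: "Variables missing more than 10% of the data will be omitted". The Introduction describes selection by the algorithms themselves: "These algorithms will cluster, classify or identify variables according to their levels of importance in predicting cancer outcomes". The unsupervised ML section adds cluster labels, "added as variables to both the training and test sets in all models".

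The supervised ML section includes a Cox-type model among the base learners: "a Cox PH model with an Elastic Net penalty will be used to estimate relative risk". Its stated uses are to supply out-of-fold predictions to the meta-learner and to inform variable importance. The section on stacking directs the performance evaluation at the stacked models.

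The abstract attaches a decision to the comparison: "The better-performing method will be implemented to develop a CRC risk prediction model".

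**The concern.** Two things change together between the two sides: the algorithm (Cox against a stacked ensemble) and the way predictors enter (preselected from literature against data-driven selection from the register variables). The Introduction discusses the comparison as one of method. It argues that ML models may outperform Cox or logistic regression, and that ML is harder to justify in some settings when the simpler methods do comparably well.

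If the ensemble performs better, the natural reading will be that ML beats Cox. The study would then adopt a stacked model whose possible loss of interpretability the authors list among the limitations. A penalised Cox model given the same candidate variables might do as well and be easier to explain in an HIV clinic. As described, that model is fitted but is not named as a comparator.

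**Working it through.** **Step 1: the two sides compared.**

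| | Cox baseline | Ensemble |
|---|---|---|
| Source of predictors | Prior knowledge and literature, simplest approach | Register variables of interest (supplemental table 1, not shown) |
| Stated restriction | Literature-based preselection | Only the rule on more than 10% missing |
| Selection | Before fitting | By the algorithms, on importance |
| Cluster labels | Unclear: the text says all models | Yes |
| Number of predictors | Not stated | Not stated |
| Test set | The 80/20 split is stated for the ML analyses only | 20% held out |

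No Cox model on the ensemble's candidate variables, and no ensemble on the Cox variables, is named as a comparator.

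**Step 2: can the predictor set alone create a gap?** The protocol gives no figure to reproduce, so this step is an illustration and every effect size is an assumption. The truth is log-linear with proportional hazards, so a flexible algorithm has nothing to gain. The same unpenalised Cox model is fitted twice, with 5 and with 20 predictors.

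Inputs:
- event rate 129.1 per 100 000 per year (protocol, Data preparation), entered as 0.00129;
- 80/20 split (protocol);
- 10 years of follow-up (the protocol's minimum median);
- 40 000 people, 5 literature predictors with log-HR 0.4 per SD, 15 extra predictors with log-HR *b* per SD, 5 replicates per setting (all assumed).

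Expected test events: 40 000 × 0.20 × 10 × 0.00129 ≈ 103 per replicate.

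As a closed-form check for rare events without estimation error, c ≈ Φ(√(V/2)), where V is the variance of the linear predictor.
- With 5 predictors: V = 5 × 0.4² = 0.80, so c ≈ Φ(0.632) = 0.736.
- With 20 predictors: V = 0.80 + 15*b*². At *b* = 0.20, V = 0.80 + 0.60 = 1.40, so c ≈ Φ(0.837) = 0.799.

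| *b* | Simulated c, 5 predictors | Simulated c, 20 predictors | Simulated difference | Closed-form difference |
|---|---|---|---|---|
| 0 (noise) | 0.751 | 0.745 | -0.006 | 0.000 |
| 0.05 | 0.734 | 0.740 | +0.006 | +0.005 |
| 0.10 | 0.722 | 0.731 | +0.008 | +0.018 |
| 0.15 | 0.737 | 0.767 | +0.030 | +0.038 |
| 0.20 | 0.741 | 0.798 | +0.056 | +0.062 |

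Differences were taken before rounding. With about 100 test events and 5 replicates, the smallest are within simulation noise.

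**Step 3: a second illustration at the planned size.** Records: 143 000 × 0.80 = 114 400 training and 143 000 × 0.20 = 28 600 test. The truth is again linear, with 6 strong and 24 weak predictors (assumed log-effects, SD 0.12) and a logistic approximation to Cox, over 12 datasets. Mean test AUC was 0.709 with 6 variables and 0.761 with all 30, a difference of 0.051 before rounding. This lies near the top of the range in Step 2.

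**Reading.** With no algorithmic advantage, a wider predictor set can change discrimination by about -0.01 to +0.06. The result depends on how informative the extra variables are.

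**The case against.** Comparing two whole strategies is a legitimate way to choose a tool. If the choice lies between a parsimonious literature-based Cox model and a data-driven ensemble, the better performer is the better performer, whatever the reason. Data-driven variable identification is also part of what the protocol means by ML. This stands, and it limits the point to the attribution of a win.

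A reader might go further and infer that the Cox model has only a few variables and the ensemble the full register set. The protocol does not say so: no covariate count is given for either side and the supplemental table is not shown. A reader might also treat the cluster labels as an advantage reserved for the ensemble. The text says they go into all models, which may include the Cox baseline.

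Nor can one say that the study is unable to answer its methodological question. The elastic-net Cox supplies most of the bridge if its own test-set performance is reported. A condensed article does not exclude that, and the full analysis plan may provide it. What remains is that the article commits only to evaluating the stacked models and names one Cox comparator, fixed with a different route to its predictors.

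Finally, the elastic-net Cox does not isolate the predictor set cleanly. It differs from the simple Cox in penalisation and data-driven selection too, and the protocol itself lists it under supervised ML. That stands and shapes the wording of the fix.

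**Conclusion.** The point holds in limited form. As described, the ensemble-versus-Cox contrast can support a choice between these two strategies. It cannot by itself attribute a gain to the ML algorithm rather than to a wider predictor set, even though the question is framed as ML against Cox and the better performer is to be implemented.

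The size is not known. The range of about -0.01 to +0.06 in c-index or AUC rests on assumed effects and predictor counts, and it concerns discrimination, whereas the protocol's primary metric is balanced accuracy. It shows that a misleading gap is possible, not how large a gap to expect. If the two variable sets turn out to be nearly the same, the concern largely disappears. A tie or a loss for the ensemble would be easier to interpret.

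**What to change.** - Keep the simple literature-based Cox as the clinical benchmark.
- Prespecify the elastic-net Cox, on the ensemble's candidate variables including cluster labels, as a second comparator.
- Evaluate the simple Cox, the elastic-net Cox and the stack on the same held-out test set with the same metrics, and report paired differences with 95% confidence intervals. State explicitly that the simple Cox is evaluated there, since the split is described only for the ML analyses.
- Claim an advantage of the stacked ensemble over Cox-type modelling only if the stack beats the elastic-net Cox.
- Describe the gap between the simple and the elastic-net Cox as the joint effect of the wider variable set and penalised selection, not of added variables alone.
- State whether the cluster labels, said to enter all models, also enter the simple Cox.

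The cost is a few sentences in the plan and one extra row in the results table. The elastic-net Cox is already to be fitted, and no further data are needed.
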